#### Screening measures

*Hurt*, *Insult*, *Threaten*, *Scream* (HITS) [30] is a 4-item instrument for DV screening. Items ask respondents how often their partner physically hurt, insulted, threatened with harm, and screamed at them. A score of 10.5 (range 4 to 20) was demonstrated to reliably differentiate victims of domestic abuse from family practice patients. The current pilot study includes parents who report a score of 7 or higher.

#### Outcome measures

*SC+ model fidelity* is assessed via client report, with clients completing a fidelity questionnaire at the end of every SC or SC+ session. The fidelity survey was adapted from the National SafeCare Training and Research Center training checklists, and the fidelity measure has been validated over the course of SC implementation [31]. Overall, monitoring of fidelity allows for measuring the effectiveness of the intervention as designed, as well as any practice changes which are naturally occurring and may need to be addressed.

*The Conflict Tactics Scales* (CTS2)*-short form* [32, 33] measures both the extent to which partners in a dating, cohabiting, or marital relationship engage in psychological and physical attacks on each other, as well as use of reasoning or negotiation to deal with conflicts. Participants are asked about the frequency of concrete acts and events within the past 6 months for their baseline CTS2 assessment, with the time frame changed to assessing if these acts and events occur within the past 2 months for the post-intervention assessment.

*The Center for Epidemiological Studies Depression Scale* (CES-D) [34] is a 20-item questionnaire, which assesses depressive symptomology. Designed as a short self-report tool, each item asks about the last week and is responded to using a 4-point format. The CES-D has high internal consistency and adequate test-retest repeatability.

*Relationship self-efficacy* (RSE) [35] is a 35-item measure evaluating relationship maintenance self-efficacy beliefs. Thirteen items relevant to the content of HR are included, across the three domains of emotional control, differentiation, and mutuality. Emotional control denotes the ability to appropriately regulate negative feelings with others. Differentiation is the capacity to assert clear interpersonal boundaries and express the need for separateness. Mutuality is defined as being able to provide care and receive support.

*Working Alliance Inventory* (WAI) [36] assesses working alliance between parents and their service providers. The current study employs the short-form, 12-item version of the WAI [37] and includes the components of goal, task, and bond. Goal is the extent to which the client and provider agree on goals of services. Task is the degree to which the client and provider agree on ways of achieving stated goals. Bond denotes mutual liking between client and provider.

*Relationship status* is a brief instrument created by the study team and intended to assess the respondent’s current intimate partner relationship or rationale for not currently engaging in one.

*Healthy relationships satisfaction* is a 14-item assessment of perspectives about the prescribed HR content, delivery of services, and service provider.

Figure 2 illustrates the framework of the research approach.

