**Methods:**

This protocol outlines a feasibility, randomized control trial to examine the potential efficacy of SafeCare+. The pilot study is divided into two phases. Components of phase one involve developing a detailed implementation and evaluation plan, including a community needs assessment, determining screening and outcome measures, and assuring all components are culturally appropriate for the target population. Phase two implements the randomization of parents, who are involved in the child welfare system and referred for in-home parenting services, into SafeCare+ or SafeCare as usual. Participants complete assessments regarding mental health, provider-parent relationship, interpersonal violence experiences, and fidelity to the intervention. Analyses will focus on improvement on target outcomes for the intervention group, as well as comparison to the control group.

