### In-home parenting programs as a unique platform to provide early intervention for DV

The primary aim of the current study is a pilot implementation and testing of culturally relevant, trauma-informed programming to lead to a reduction of family violence, a resulting increase in family stability, improved communication, and a healthy home environment for children in Latinx families with co-occurring DV and child maltreatment. Specific objectives include the following:
Increased access to culturally specific, trauma-informed, evidence-informed interventions.Increased understanding of the needs of the target population and how to meet them.Improved collaboration, policies, and practices for effectively meeting the needs of the target population.Reduced incidents of DV at case closure.Improved mental health at case closure.Improved communication skills at case closure.

The intervention being implemented is SafeCare+ (SC+), an evidence-based (EB) training curriculum for parents referred for child maltreatment, enhanced with the healthy relationships (HR) module. SafeCare (SC) has been shown to be widely accepted among the Latinx community [24]. The HR enhancement is a promising practice that may prevent and/or reduce family violence among Latinx families. The study will test the efficacy of the SC+ model, contributing to the DV field’s evidence base of effective practices that improve outcomes for Latinx families impacted by both DV and child maltreatment. The evaluation of the pilot implementation will impact and inform advocacy and practice change.

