### Design

The pilot study is divided into two phases. During phase one, the first year of the study, community and academic partners collaborate to develop a detailed evaluation plan. The evaluation centers on the effective implementation of SC+ and measurement of relevant outcomes during phase two of the project—the RCT, pilot study. Components of phase one include (1) a community needs assessment, (2) refining the target population, (3) designing the evaluation plan, (4) determining screening and outcome measures, (5) conducting focus groups with key stakeholders, including DV providers and Latinx survivors, to assure that the chosen interventions and screening and assessment tools are culturally appropriate for the target population, and (6) ensuring the proper training of direct service staff. For phase two, the RCT pilot study will enroll at least 160 parents either into SC or SC+, allocating a minimum of 80 parents per condition. Parents will be randomized to SC or SC+ and within home visitor, such that every other eligible parent will be assigned to SC or SC+ within home visitor. The nested structure will be accounted for in multi-level analyses, see Fig. 1 (SafeCare+ study flow diagram).

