### Data collection points for outcome measures

Data collection for SC/SC+ fidelity will be conducted at each session of the intervention, throughout the course of service delivery. The CES-D is assessed at intake into SC, at the end of the intervention, and at the end of the study. The CTS-2, WAI, RSE, and relationship status measures are assessed at the beginning and conclusion of receiving the intervention (i.e., the HR curriculum, or the comparison time frame for the control condition). HR satisfaction is assessed at the conclusion of receiving the intervention, see Fig. 3 (SPIRIT figure for SafeCare+ trial for data collection timings).

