### Data analyses

#### Quantitative analyses

Primary analyses will be based on generalized linear mixed models [38–40]. Mixed models are necessary for analyzing data from the proposed project because the data will have a three-level, hierarchical data structure in which measurements over time are nested within clients and clients are nested within provider. The models tested involve both fixed and time-varying covariates. All models will be multivariate in nature (i.e., testing all predictors simultaneously). Significance tests will focus on individual regression coefficients from the models. In addition, the final data set will offer rich opportunities for auxiliary or secondary analyses, including exploring the role of fidelity for mediating client outcomes. Dependent variables will be changed in (1) reports of DV on the CTS, (2) depression, (3) relationship self-efficacy, and (4) indicators of fidelity to SC and SC+.

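### CTS2 recall is 6 months at baseline and 2 months at follow-up, so change within an arm shows a fall in violence even if nothing changed; the between-arm comparison is not biased

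*Protocol article*

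**What the plan says.** Under Outcome measures, the protocol article sets the baseline window: "Participants are asked about the frequency of concrete acts and events within the past 6 months for their baseline CTS2 assessment". For the second assessment the window is shortened, "with the time frame changed to assessing if these acts and events occur within the past 2 months for the post-intervention assessment".

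Under Quantitative analyses, the first dependent variable listed is change in CTS reports: "Dependent variables will be changed in (1) reports of DV on the CTS" (we read the garbled verb as change in these reports). The model class is given as "Primary analyses will be based on generalized linear mixed models", with tests on individual regression coefficients. No link, offset, annualisation or scoring rule is stated.

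Two places plan a conclusion about change over time. The abstract's Methods paragraph says "Analyses will focus on improvement on target outcomes for the intervention group, as well as comparison to the control group", and the specific objectives include "Reduced incidents of DV at case closure".

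Under Data collection points, the CTS2 visits are the same in both arms: "assessed at the beginning and conclusion of receiving the intervention (i.e., the HR curriculum, or the comparison time frame for the control condition". The Design section has "allocating a minimum of 80 parents per condition".

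**The concern.** The baseline window is three times as long as the follow-up window, so a difference between the two scores mixes exposure time with any real change in behaviour. The problem is specific to the CTS2; the CES-D, for example, asks about the last week.

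This is more than detail left to a fuller document. The article fixes both windows, fixes change between them as an outcome, and names improvement in the intervention group as a focus of analysis. A time coefficient or a paired comparison on the CTS2 would show a fall in both arms with no effect of either programme. The objective of fewer incidents could then appear met because of the questionnaire alone, in a pilot whose findings are meant to inform the decision on a definitive trial.

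The wording also moves from frequency at baseline to whether acts occur at follow-up. If the response format changed as well, the scores are even less comparable; the article does not settle this.

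**Working it through.** **The plan's own figure.** The Sample size section gives 160 parents for a medium Cohen's d, without alpha, power or dropout, so it cannot be strictly reproduced. Assuming d = 0.5 and two-sided alpha 0.05, 63 per arm gives 80% power and 85 per arm gives 90%. For 80 per arm, power = Φ(0.5 × √(80/2) − 1.96) = Φ(1.20) = 88.5%. The point does not rest on this figure.

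**Step 1: raw counts, violence unchanged.** At a constant rate λ per month, expected counts are 6λ at baseline and 2λ at follow-up. The ratio is 2/6 = 0.33, a 67% fall at any λ. In a log-link model without an offset, the time coefficient would be ln(1/3) = −1.10 with no true change.

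**Step 2: any-event score.** Prevalence is 1 − exp(−6λ) at baseline and 1 − exp(−2λ) at follow-up. The rates are assumptions:
- λ = 0.1: 45% to 18%
- λ = 0.25: 78% to 39%
- λ = 0.5: 95% to 63%
- λ = 1: 99.8% to 86.5%
- λ = 2: about 100% to 98%

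So the fall is large when acts are infrequent and nearly vanishes when everyone has frequent acts. If rates differ strongly between people (gamma-Poisson, shape 0.5), a fall remains at a mean of 2 per month: 80% to 67%.

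**Step 3: size in SD units.** Gamma-Poisson counts were simulated with mean rates of 0.1 to 4 per month and shapes of 0.5 to 2. The apparent change is 0.35 to 0.91 baseline SD on counts and 0.38 to 1.32 on an assumed 0–6 frequency category score. It is at least 0.5 SD in 24 of the 36 combinations of setting and score.

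**Step 4: null trials.** There were 80 parents per arm, 4,000 runs in each of three settings, the category score, no provider clustering and no true change:
- within-arm paired test, 6 versus 2 months: rejects in 99.9% to 100%
- within-arm paired test, 2 versus 2 months: rejects in 4.5% to 5.1%
- between-arm test of the change score, 6 versus 2 months: rejects in 4.6% to 5.0%

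**Step 5: precision of the arm comparison if raw counts are subtracted.** Let rates have mean m and variance v between people, constant over time.
- Var(baseline) = 6m + 36v
- Var(follow-up) = 2m + 4v
- Covariance = 6 × 2 × v = 12v
- Var(change) = 8m + 40v − 24v = 8m + 16v = 4 × (2m + 4v)

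The variance of change is 4 times the follow-up variance for any m and v, so its SD is twice as large. A true 0.5 SD difference on the follow-up score becomes 0.25 SD on the change score. Power with 80 per arm is Φ(0.25 × √40 − 1.96) = Φ(−0.38), about 35%. The follow-up score alone gives about 88%. With baseline as covariate and an assumed correlation of 0.5, residual variance is 1 − 0.25 = 0.75, the effective d is 0.5/√0.75 = 0.577, and power is about 95%. The step from 88% to 95% comes from covariate adjustment, not from the windows.

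**The case against.** The best defence is that the trial is randomised. The Feasibility outcomes section says limited effectiveness is judged by comparing the groups, and both arms answer over the same windows at the same visits. This stands: the artefact cancels in the mean, and step 4 shows the nominal error rate. A reader might infer that the trial's test of SafeCare+ on violence is biased; the documents do not support that.

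A reader might also infer that the arm comparison certainly loses most of its power. That too goes beyond the text. The phrase about change need not mean raw subtraction, and the article names only a model class. In a log-link model the time term absorbs the constant 1/3 ratio and the arm-by-time term stays interpretable, which would largely avoid the loss. The 35% in step 5 applies only to subtraction or an identity scale.

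There is also a reason for the short follow-up window. The Discussion says the added curriculum lengthens services by about 2 months, so a 6-month recall at its end would reach back before it began. That explains the follow-up window, but not the longer one at baseline.

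Finally, the 67% is for raw counts and no scoring rule is given. The eligibility criteria deliberately include families with psychological violence, where frequent acts are plausible, and an any-event score might then move little. That limits the size of the artefact for one kind of score but does not remove it for counts or frequency categories.

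**Conclusion.** The concern holds for change within an arm. The 2/6 ratio comes directly from the two stated windows, and the 67% fall in expected counts needs only a constant rate. The fall on other scores depends on assumed event rates and scoring, hence the ranges. Nothing in the article rescales for the difference in recall, while within-group improvement and fewer incidents are planned conclusions.

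For the arm comparison there is no bias, only a conditional loss of precision that rests on raw subtraction or an identity scale, the constant-rate model and an assumed 0.5 SD effect.

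This should be fixed. It falls short of a defect that invalidates the trial: it is a feasibility pilot, the CTS is one of four dependent variables, and none is designated primary.

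**What to change.** 1. Define the CTS2 outcome as the 2-month post-intervention score compared between arms, with the baseline score as a covariate and not subtracted. This also works for parents already enrolled. If actual counts are recorded at both visits, an alternative is to model rates with a log recall-length offset, which brings the expected rate ratio under no change from 0.33 to 1.0.
2. State that no within-arm claim of reduced violence will be made from the 6-month and 2-month scores.
3. Optionally, for parents still to be enrolled, add a 2-month reference period at baseline and keep the 6-month question for everyone. Dropping the 6-month question during ongoing recruitment would leave a baseline covariate that is not comparable across enrolment periods.

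Items 1 and 2 cost only wording in the analysis plan. Item 3 makes the baseline questionnaire slightly longer, and a 2-month baseline captures fewer events.

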**Fig. 2 Fig2:**
[figure not shown]
Logic model for the SafeCare+ pilot study

### Data collection points for outcome measures

Data collection for SC/SC+ fidelity will be conducted at each session of the intervention, throughout the course of service delivery. The CES-D is assessed at intake into SC, at the end of the intervention, and at the end of the study. The CTS-2, WAI, RSE, and relationship status measures are assessed at the beginning and conclusion of receiving the intervention (i.e., the HR curriculum, or the comparison time frame for the control condition). HR satisfaction is assessed at the conclusion of receiving the intervention, see Fig. 3 (SPIRIT figure for SafeCare+ trial for data collection timings).

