### Eligibility criteria

Participants will be included in the RCT pilot study if the following criteria are met: (1) currently receiving SC services, meeting ICT inclusion criteria; (2) a primary caregiver identifying as Latinx; (3) over 18 years of age; and (4) at risk for DV. The criterion for risk of DV was intentionally set to be broadly inclusive of families who are struggling with psychological violence. Clients will be excluded from participation if there are immediate safety risks in the family.

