### Interventions

#### Control group: SafeCare

SafeCare (SC) is an EB parenting curriculum, delivered via home visitation, for parents with preschool or school-age children who are at risk of or have been reported for child neglect, physical abuse, or both. SC targets improvement in skills related to home safety, health, and parent-child interaction [26]. These modules include a baseline assessment, training in knowledge and skills, and follow-up assessments to monitor change. Delivery of the program is based on the principles of behavioral analysis—service providers are trained to model skills, engage in ongoing measurement of observable behaviors, and to give constructive feedback during skills practice. SC program completion typically takes 18 to 20 home visiting sessions over 6 months. A number of studies attest to SC effectiveness and provide evidence on improved parental outcomes, including better management of their child’s health, increased home safety, and more positive and sensitive parent-child interaction [26–28]. In addition, SC has been demonstrated to be efficacious for reducing CWS recidivism relative to usual care [29]. Participants randomized to the control group will receive the EB, SC as usual.

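### The only CES-D before the intervention is taken at SafeCare intake, so within-arm depression change can include earlier SafeCare and does not isolate the period in which the arms differ

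*Protocol article*

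**What the plan says.** All references are to the protocol article.

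- *Eligibility criteria*: the first criterion is that the parent is "currently receiving SC services, meeting ICT inclusion criteria". No position within the SafeCare (SC) course is given.
- *Design*: allocation is among parents who meet the criteria; "every other eligible parent will be assigned to SC or SC+ within home visitor".
- *Data collection points for outcome measures*: "The CES-D is assessed at intake into SC, at the end of the intervention, and at the end of the study". For the other pre/post measures, "The CTS-2, WAI, RSE, and relationship status measures are assessed at the beginning and conclusion of receiving the intervention". That section defines the intervention as the HR curriculum or, in the control arm, the comparable time frame.
- *Outcome measures*: for the CES-D, "each item asks about the last week".
- *Control group: SafeCare*: "SC program completion typically takes 18 to 20 home visiting sessions over 6 months". The *Discussion* adds that HR lengthens services by 30%, about 2 months.
- *Quantitative analyses*: "Dependent variables will be changed in (1) reports of DV on the CTS, (2) depression", followed by relationship self-efficacy and fidelity.
- *Abstract, Methods*: the analyses are to look at improvement within the intervention group as well as the comparison with control.

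**The concern.** The schedule ties four pre/post measures to the start of the HR period but ties depression to entry into SC. A CES-D score describes a single week. If a parent is screened and allocated some way into SC, that week lies before SC sessions that parents in both arms have already received, and before the choice of arm.

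Two things are at stake. The first is the within-arm reading. Improvement in depression among SC+ parents would include whatever happened during earlier SC and with the passage of time since child-welfare intake. Randomization does not protect a within-arm change from this. The second is precision. A more distant baseline usually correlates less with the outcome, and the distance may differ from parent to parent, so the arm comparison gains less from using it.

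**Working it through.** **1. The plan's own figure.** *Sample size* gives 160 parents (80 per arm under *Design*) as adequate for a medium Cohen's d, with no alpha or power stated. Taking d = 0.5 and two-sided alpha 0.05 as assumptions, with no clustering or dropout, n per arm = 2(z₀.₉₇₅ + z_power)²/d².

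- 80% power: 2(1.960 + 0.842)²/0.25 = 62.8, so 63 per arm.
- 90% power: 2(1.960 + 1.282)²/0.25 = 84.1, so 85 per arm.
- 80 per arm gives 88.5% power.

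The stated size is compatible with a medium effect. There is no stated power to reproduce, and the timing point does not depend on it.

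**2. Order of events.** Parents must already be in SC to be eligible, and allocation is among eligible parents. So SC intake, where the CES-D is taken, comes no later than allocation. Allocation comes no later than HR start, where the other four measures are taken. The text lists no CES-D at allocation or at HR start.

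**3. Length of the gap.** Let g be the time from SC intake to HR start and h the HR period. From the protocol, g lies between 0 and about 6 months, and h is about 2 months (0.30 × 6 = 1.8).

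- Time between first and end-of-intervention CES-D = g + h: from 0 + 2 = 2 months to 6 + 2 = 8 months.
- Time between the two administrations of the other measures = h, about 2 months.
- Share of the CES-D window before HR = g/(g + h): from 0 to 6/8 = 75%.

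The upper end is a limit. A parent who has completed a typical 6-month course would hardly still be receiving SC.

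**4. What the change measures.** Let a be the mean CES-D change from SC intake to allocation, b the mean change after allocation with SC alone, and δ the added effect of SC+.

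- Change from intake: SC+ arm a + b + δ; SC arm a + b; difference δ.
- Change from an enrolment baseline: SC+ arm b + δ; SC arm b; difference δ.

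With sound allocation, a is equal in the two arms in expectation and drops out of the contrast. It does not drop out of the within-arm change.

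**5. Precision.** With outcome SD 1 and baseline-outcome correlation r, the baseline-adjusted residual variance is 1 − r². The protocol gives no correlations. The values here are assumptions: 0.6 for a CES-D at enrolment, and 0.5 or 0.4 for one at intake.

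- r = 0.6: 1 − 0.36 = 0.64.
- r = 0.5: 1 − 0.25 = 0.75; 0.75/0.64 = 1.17, so +17%.
- r = 0.4: 1 − 0.16 = 0.84; 0.84/0.64 = 1.31, so +31%.

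For raw change scores the variance is 2(1 − r): 0.8, 1.0 and 1.2, so +25% and +50%.

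In power terms (80 per arm, baseline-adjusted, same simplifications as step 1), r = 0.6, 0.5 and 0.4 give 97.7%, 95.5% and 93.2% at d = 0.5, and 66.0%, 59.1% and 54.4% at d = 0.3.

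**The case against.** The article does not say when in SC a parent is screened or allocated. The abstract speaks of randomizing parents referred for in-home services, and SC+ is described as an enhanced version of the SC program. Both fit allocation close to SC intake, in which case the intake CES-D is a proper pre-allocation baseline. The flow diagram and the SPIRIT figure, which are not shown here, may settle this. An objective framed as improved mental health at case closure also gives a reason to measure depression from the start of services. All of this stands. It means that the gap is possible and unbounded by the text, not that it is known to be long.

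Four stronger readings are tempting, and the documents do not support them:

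- *That the depression baseline is months old.* The interval may be near zero.
- *That the estimated effect of SC+ on depression is biased.* SC before allocation is common to both arms in expectation, so the contrast still estimates the effect after allocation.
- *That variance rises by half.* That figure pairs the lowest assumed correlation with unadjusted change scores.
- *That CTS2 isolates the HR period and depression alone does not.* The CTS2 asks about the past 6 months at baseline and the past 2 months afterwards, so its baseline also reaches back beyond HR start.

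What the objection does not remove is the explicit list of three CES-D time points with none tied to allocation or HR start, together with a planned analysis of within-arm improvement.

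**Conclusion.** The point holds as a worthwhile and cheap improvement to a stated schedule. It does not invalidate the arm comparison. Within-arm change in depression can include change during earlier SC, over an interval from near zero to at most about 6 months, and so does not isolate the period in which the arms differ. The between-arm contrast is unbiased on this count, provided that allocation itself is sound. It may lose some precision: about 17% to 31% more baseline-adjusted residual variance if the correlations are 0.6 against 0.5 or 0.4, and nothing if allocation occurs at intake. The true size cannot be known from the article.

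**What to change.** 1. Give the 20-item CES-D at enrolment to every parent in both arms, before the allocation is made known, and use that score as the depression baseline. If enrolment falls at SC intake, the intake form already serves.
2. Keep the SC-intake CES-D as an additional covariate or as an earlier time point in the mixed model.
3. Record the interval and the number of SC sessions completed from SC intake to allocation, and tabulate both by arm.
4. For parents already enrolled without the new form, model actual time since SC intake.
5. In reporting, base statements about the effect of SC+ on depression on the between-arm contrast. Even with the new baseline, within-arm change still includes the effect of SC after allocation (b in the working).

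The cost is one more 20-item self-report per parent, on the tablet that providers already bring to each visit. The added burden is small but real, especially for the parents with literacy challenges whom the *Discussion* mentions. *Data Availability* describes recruitment as ongoing, so later enrollees could still be covered at the time of writing.

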### Measures

All measures are client-reported and will be collected via a secure, web-based data entry system, on an internet-enabled tablet that service providers bring to each visit. At the end of each SC or SC+ visit, providers activate the participant survey by logging into the secure web-based data entry system on their assigned tablet computer and selecting the appropriate client identifier (a number randomly generated by the secure system). Once the survey has been activated, the service provider will give the client the tablet computer to complete the measures privately. In the infrequent circumstance that two parents are simultaneously participating in services, the assessments are completed by each, separately, while the other parent is engaged with the home visitor. All measures are available in both English and Spanish.

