A primary aim of the RCT, pilot study is to demonstrate the effectiveness of the HR curriculum. A significant advantage of the design of the pilot study is the embedded nature of the RCT into a larger study. Substantial infrastructure support with regard to recruitment and data collection serve as an important foundation to success. A primary challenge of the RCT pilot study is that the inclusion of the HR curriculum into the existing service delivery system extends the length of services by 30% (~ 2 months). As a result, parents assigned to the intervention condition may not actually receive the entirety, or in some cases any, of the intervention due to the service requiring more time than the CWS timeline for length of service delivery. A study limitation is that parents with literacy challenges may have difficulty completing the outcome measures to determine effectiveness. In addition, the cultural appropriateness of outcome measures is a primary consideration. The first phase of the study is intended specifically to collaborate with technical assistance providers, community partners, and Latinx parents to ensure that the data collection efforts are aligned with the trauma-informed approach of the study.

Results from this study will inform the ways in which the CWS system of care may be strengthened to sustain long-term safety and well-being of children, while also providing efficacy data for a large, system-wide randomized control trial of the intervention. In addition, service providers are gaining multiple experiences with the provision of trauma-informed practice and intentional approaches to working with children and families with histories of DV. This pilot study provides an important foundational step to determining how DV services may be integrated into CWS home visitation programs, setting a platform for continued work with this population.

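### CTS2, WAI, RSE and relationship status are timed by receipt of HR, which some SC+ parents are expected not to reach, and by a control window that the article does not define

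*Protocol article*

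**What the plan says.** The section on data collection points sets four measures (CTS2, WAI, RSE and relationship status) "at the beginning and conclusion of receiving the intervention (i.e., the HR curriculum, or the comparison time frame for the control condition". It refers to Fig. 3 for the timings; that figure is not in the text at hand. Depression is handled differently: "The CES-D is assessed at intake into SC, at the end of the intervention, and at the end of the study". Of these three CES-D points, the first and last do not depend on HR. For satisfaction, "HR satisfaction is assessed at the conclusion of receiving the intervention".

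The Discussion reports that adding HR "extends the length of services by 30% (~ 2 months", and that as a result "parents assigned to the intervention condition may not actually receive the entirety, or in some cases any, of the intervention", because the service may need more time than the child welfare timeline allows. The section on the control group says that "SC program completion typically takes 18 to 20 home visiting sessions over 6 months". Under Measures, data capture is tied to service contacts: "At the end of each SC or SC+ visit, providers activate the participant survey".

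The quantitative analysis section names four dependent variables: DV on the CTS, depression, relationship self-efficacy and fidelity. It plans three-level mixed models. Among the objectives is "Reduced incidents of DV at case closure".

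**The concern.** A randomised comparison needs outcomes from everyone allocated, at times that do not depend on what happened after allocation. Here the trigger for CTS2 and RSE in SC+ is starting and finishing the module under test, and the article itself expects some parents to do neither. Control parents have no HR module to start or finish. If the schedule is followed literally, CTS2 and RSE can be missing for a reason that exists in one arm only and that may be related to prognosis. These are two of the four dependent variables. The results are meant to supply efficacy data for a system-wide trial, and an outcome that was never collected cannot be recovered at the analysis stage.

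The same anchor affects satisfaction. Collected only when HR concludes, it leaves out parents who began HR and left, whose views matter for acceptability.

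**Working it through.** **Step 1. Which parents have a defined CTS2/RSE time point?** Reading the schedule and the Discussion together:

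| Parent | Baseline | Follow-up |
|---|---|---|
| SC+, completes HR | start of HR | end of HR |
| SC+, starts HR, does not finish | start of HR | none stated |
| SC+, never starts HR | none stated | none stated |
| SC | start of an undefined window | end of that window |

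A mixed model can keep the second group, under a missing-at-random assumption. A parent in the third group, with neither measurement, contributes nothing to the CTS2 or RSE model.

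**Step 2. The plan's own sample size.** The article gives 160 parents, at least 80 per arm, for a medium Cohen's d. Alpha and power are not stated, so 160 cannot be strictly reproduced. Assume d = 0.5, two-sided alpha 0.05, no clustering and no loss. Then n per arm = 2(1.96 + z)²/d², which gives 63 for 80% power and 85 for 90%. With 80 per arm, power is 0.885. The stated size is compatible with its claim on these terms, and this point does not rest on it.

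**Step 3. Bias if only HR completers are analysed.** Let f be the share of SC+ parents who do not complete HR, and g the gap in mean outcome, in SD, between completers and the rest. With no treatment effect, the full SC+ mean differs from the completers' mean by f × g, so that is the size of the bias. With all 80 controls observed, SE = √(1/80 + 1/(80(1 − f))). The article gives neither f nor g; both are assumed.

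| f | SC+ observed | Bias, g = 0.25 | Bias, g = 0.5 | Bias, g = 0.75 | Type I error, g = 0.5 |
|---|---|---|---|---|---|
| 10% | 72 | 0.025 | 0.05 | 0.075 | 0.06 |
| 20% | 64 | 0.05 | 0.10 | 0.15 | 0.09 |
| 30% | 56 | 0.075 | 0.15 | 0.225 | 0.14 |
| 40% | 48 | 0.10 | 0.20 | 0.30 | 0.20 |

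For example, at f = 20% and g = 0.5, SE = √(1/80 + 1/64) = 0.168, bias/SE = 0.10/0.168 = 0.60, and a nominal 5% test rejects about 9% of the time.

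**Step 4. Timing.** 30% of 6 months is 0.3 × 6 = 1.8 months, which agrees with the stated figure of about 2. The position of HR in the service sequence is not given. If HR follows the usual modules, it runs from about month 6 to month 8. A control window at the same time since intake would then fall after ordinary SC visits have ended, and visits are where surveys are activated. A control window placed within those visits would be earlier, by up to about 2 months. So unequal timing is possible but conditional.

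**Step 5. What as-allocated analysis costs.** Here let f be the share of SC+ parents who receive no benefit because they get no HR. The effect becomes 0.5(1 − f). With 80 per arm:

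| f | Diluted d | Power | n per arm for 80% power |
|---|---|---|---|
| 0% | 0.50 | 0.885 | 63 |
| 10% | 0.45 | 0.81 | 78 |
| 20% | 0.40 | 0.72 | 99 |
| 30% | 0.35 | 0.60 | 129 |
| 40% | 0.30 | 0.48 | 175 |

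**The case against.** The strongest reply is that the text leaves a gap and does not state a bad rule. Several stronger readings are tempting, and the article does not support them.

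- *That SC+ parents without HR have no CTS2 or RSE data.* Nothing says they go unmeasured. Their time point is simply not given, and Fig. 3 or the full protocol may supply it.
- *That the arms are measured at different times.* Giving controls a counterpart window signals an intended match. The supportable criticism is that the window is undefined.
- *That the comparison is SC+ completers against all controls.* The service-length limit is not described as applying to one arm only. If the control window is late, some controls whose visits have ended would miss it too. If it is early, that loss is smaller but timing differs. The two harms trade off, so both cannot be assumed in full.
- *That bias favours SC+.* The direction is not established. The outcome is change, and a later SC+ baseline might leave less room to improve.
- *That case closure is a different time point from the assessments.* If HR comes last, its conclusion may coincide with closure.

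It is also fair that CES-D has HR-independent points, that acceptability rests partly on focus groups, and that this is a pilot that openly discloses non-receipt.

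These replies limit the claim but do not remove it. The article states an anchor and, separately, expects some parents to miss it. Nothing in the visible text reconciles the two for CTS2 or RSE.

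**Conclusion.** The point holds in a limited form. CTS2, WAI, RSE and relationship status are anchored in SC+ to an event after randomisation that the article expects some parents not to reach, and in SC to a window that it does not define. Followed as written, this leaves some SC+ parents without a defined follow-up, and some without a defined baseline either. The consequence is a risk of arm-dependent missing data on CTS2 and RSE, and possibly of unequal timing.

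The illustrative size is 0.10 to 0.15 SD for 20% to 30% non-completion, against a target taken here as d = 0.5. It rests on an assumed g of 0.5 SD, on analysing completers only, on complete control data and on ignoring clustering. It shows what could happen and does not estimate what will.

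**What to change.** 1. Take baseline CTS2, RSE and relationship status at the eligibility contact, before the arm is revealed.
2. Take follow-up at the same stated interval from allocation in both arms, whether or not HR was started or finished. This also replaces the undefined control window.
3. Add CTS2 and RSE to the end-of-study point at which CES-D is already collected, and say how parents whose visits have ended will be reached.
4. Analyse all parents as allocated.
5. Collect HR satisfaction from every parent with at least one HR session.

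The cost is a slightly longer questionnaire at the eligibility and end-of-study contacts, plus some effort to reach parents after visits stop; the article does not show that the end-of-study contact already does this. The larger cost is power. At d = 0.5 and 80 per arm, before clustering and loss, as-allocated power falls from about 0.885 to about 0.72 at 20% non-receipt and 0.60 at 30%. The plan should state this dilution openly. Recording the non-receipt rate would also be useful for planning the larger trial.
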